### 3.4. Randomization and Blinding Procedures

The allocation concealment will be ensured through the randomization process. Sealed, opaque envelopes will be used, numbered consecutively by an Assistant Professor of the Laboratory of Advanced Physiotherapy, University of West Attica, who will not participate in any other process of the study. Participant assignment will be concealed from both participants and evaluators, while the principal investigator will be informed, in accordance with a single-blinding procedure.

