## 3. Methods

### 3.1. Study Design

This study is structured as a two-arm, parallel-group randomized controlled trial, conducted in line with the CONSORT guidelines and the SPIRIT recommendations for interventional trial protocols [19]. The study’s design is presented in Figure 1. The protocol has been prospectively registered on ClinicalTrials.gov (NCT07131397).

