### 3.5. Participants and Eligibility Criteria

Adults aged 18–70 years with a confirmed diagnosis of gastroesophageal reflux disease by a gastroenterologist are eligible to participate (inclusion criteria). Selection and initial assessment will be done by a physiotherapist [21,22]. Exclusion criteria include pregnancy, previous gastric or duodenal surgery, systemic connective tissue diseases, tuberculosis, and diagnosed mental disorders [23].

Participants’ characteristics: The sample will comprise participants of all genders, including both males and females with diagnosed GERD, from the Attica region. The minimum sample size was determined using the G*Power software (version 3.1.9.7), based on an effect size of 1.3 for MIP reported by Fonseca et al. (2014) [24]. Based on an effect size of 1.3, a statistical power of 0.80, and an α level of 0.05, the minimum required sample size was 22 participants. Accounting for a potential 15% dropout rate, the final minimum sample size was set at 25.

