#### 3.6.1. Primary Outcomes

Inspiratory muscle strength is the primary outcome of the study. Maximal inspiratory pressure (MIP) will be used as an indicator of overall inspiratory muscle strength, reflecting the maximum static pressure generated against an obstructed airway. This measure has been chosen for its clinical relevance in identifying diaphragmatic weakness and monitoring adaptations induced by training [34]. The ATS/ERS guidelines recommend performing 3 measurement attempts. According to them, an absolute maximum inspiratory pressure value at the mouthpiece of 80 cmH_2_O usually excludes clinically significant weakness of the inspiratory muscles. In older ages, the limit for men is 60 cm H_2_O and for women, it is 40 cmH_2_O [34]. The measurement of maximum expiratory pressure will be performed using the same equipment, measures the strength of the expiratory muscles and is performed with the patient in a sitting position and closed nose. A maximal inspiratory effort is commanded for 1–2 s and repeated 3–8 times. In women, the normal limit is 120 cmH_2_O of mercury, while in men, it is 150 cm of mercury [35]. In addition, maximal dynamic inspiratory pressure will be assessed using the S-index. The S-index is a new non-invasive method for the dynamic assessment of inspiratory muscle strength. The measurement is performed using an electronic inspiratory muscle training device that applies conical flow resistance as a loading method. The measurement includes 10 maneuvers, with the participant being encouraged to make a maximum effort up to the total lung capacity. At the beginning of the measurement, a warm-up session (one set of 30 breaths at 40% of S-index) has been included to enhance pulmonary function and attenuate the ‘learning effect’ of repeated measurements [27]. This outcome provides information on inspiratory muscle performance under conditions that more closely resemble functional breathing tasks and may be more sensitive to training-related changes than static measurements alone [27,36]. The average value of the S index in healthy populations is 159 cmH_2_O in men and 115.29 cmH_2_O in women [28].

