## 4. Analytical Approaches for Statistical Evaluation of the Data

Statistical analyses will be performed using the Statistical Package for the Social Sciences (SPSS, version 29; IBM Corp., Armonk, NY, USA). Prior to inferential analysis, data will be screened for completeness and distributional characteristics. The normality of continuous variables will be examined using the Shapiro–Wilk test. Descriptive statistics will be used to present and summarize participants’ characteristics.

To evaluate the reliability of repeated measurements across the assessment time points, intraclass correlation coefficients will be calculated for the primary outcome measures [44].

The primary analysis will focus on determining whether changes in outcome measures over time differ between the experimental groups. Repeated measures 2 × 3 ANOVA with Bonferroni correction will be used to examine interaction effects between group allocation (IMT vs. sham IMT) and time (T1, T2, T3) [44]. Additionally, we will evaluate differences between groups at each time point. Assumptions of homogeneity of variance will be assessed prior to model interpretation. Statistical significance will be set at an alpha level of 0.05 for all analyses.

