**Enrollment Procedures**					
Eligibility screening	X				
Informed consent obtained	X				
Collection of demographic data	X				
Inclusion of participants in study	X				

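### The planned arm comparisons at each visit name no covariate, so on S-index they carry avoidable between-sex variance; the primary group-by-time test does not

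*Protocol article*

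**What the plan says.** - **Participants (section 3.5):** "The sample will comprise participants of all genders, including both males and females with diagnosed GERD". The expected split is not given.
- **Sex difference on a primary outcome (section 3.6.1):** "The average value of the S index in healthy populations is 159 cmH_2_O in men and 115.29 cmH_2_O in women". For MIP the same section gives only lower limits for older people, 60 cmH2O for men and 40 for women. These are cut-offs, not means.
- **Data available before allocation (Table 1):** "Collection of demographic data" is scheduled at enrolment.
- **Allocation (section 3.4):** "Sealed, opaque envelopes will be used, numbered consecutively by an Assistant Professor". How the sequence is generated, and whether there are blocks or strata, is not described.
- **Analysis (section 4):** "Repeated measures 2 × 3 ANOVA with Bonferroni correction will be used to examine interaction effects between group allocation (IMT vs. sham IMT) and time". The section then adds: "Additionally, we will evaluate differences between groups at each time point". Neither sex nor the baseline value is named as a covariate.

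**The concern.** MIP and S-index are strength measures, and the protocol's own reference figures show S-index differing markedly between men and women. A comparison of arm means at one visit, with no covariate, puts all of that difference into the error term. In a trial of 25 to 30 people the sex mix of the two arms can also differ by several people by chance, which moves the observed arm difference at that visit.

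Readers will look to the T2 comparison to judge whether training beats sham, and to the T3 comparison to judge whether the effect lasts. Lost precision there makes a real difference harder to see, although the characteristic that would recover some of it is known at enrolment.

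**Working it through.** **Inputs from the document.** S-index means are 159 and 115.29 cmH2O (section 3.6.1, healthy people). The sample size is 22 before dropout and 25 after (section 3.5), or 30 (Abstract). The design is a "two-arm, parallel-group randomized controlled trial".

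**Assumptions.** Allocation 1:1; about half the participants men; within-sex SD of S-index 20 to 35 cmH2O; a training gain of 25 cmH2O over sham for the power figures; within-sex correlation of 0.70 between T1 and T2. The document gives none of these.

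**1. The plan's own figure.** "Based on an effect size of 1.3, a statistical power of 0.80, and an α level of 0.05, the minimum required sample size was 22". A two-sided two-sample t-test at d = 1.3 has power 0.785 with 10 per arm and 0.826 with 11 per arm, so 22 is reproduced. It rests on MIP.

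**2. Sex gap.** 159 − 115.29 = 43.71 cmH2O.

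**3. Share of single-visit variance.** With half men, the between-sex variance is (43.71/2)² = 21.855² = 477.6. With within-sex SD s, the share is 477.6/(s² + 477.6), and removing it cuts the SD by 1 − s/√(s² + 477.6).

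| Within-sex SD (assumed) | Total SD | Share due to sex | Cut in SD |
|---|---|---|---|
| 20 | 29.6 | 54% | 32% |
| 25 | 33.2 | 43% | 25% |
| 30 | 37.1 | 35% | 19% |
| 35 | 41.3 | 28% | 15% |

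**4. Chance imbalance.** With equal arms, the number of men in one arm is hypergeometric. The probability that the arms differ by at least 3 men is:
- N = 30: 0.47 with 15 men, 0.27 with 14 or 16, 0.26 with 12 or 18.
- N = 22: 0.40 with 11 men, 0.20 with 10 or 12, 0.18 with 8 or 14.

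The spread arises because an odd number of men allows only odd differences (1, 3, 5 and so on) and an even number only even ones. A difference of 3 men shifts the arm difference in mean S-index by 43.71 × 3/15 = 8.7 cmH2O at N = 30, or 43.71 × 3/11 = 11.9 cmH2O at N = 22.

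**5. Effect on the T2 comparison (simulation, 15 per arm, gain 25 cmH2O).** Adding sex to the unadjusted comparison:
- SD 25: the SD of the arm difference falls from about 12 to 9 cmH2O, and power rises from about 0.50 to 0.73.
- SD 35: the SD falls from about 15 to 13 cmH2O, and power rises from about 0.36 to 0.46.

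**6. Effect on the primary test.** If sex adds a constant amount c to a man's S-index at every visit, his change from T1 to T2 contains c − c = 0. Simulation agrees. Adding sex to the change comparison moves power from 0.931 to 0.922 (SD 25, correlation 0.70) and from 0.672 to 0.656 (SD 35, correlation 0.70), so there is no gain.

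**7. Baseline adjustment at T2.** At correlation 0.70, adjusting for baseline alone gives power 0.941 at SD 25, and 0.948 with sex added. At SD 35 it gives 0.712 with or without sex. Baseline adjustment thus does more than sex alone (0.73 and 0.46), and sex then adds about 1 point or less.

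**8. Type I error.** Simulated under no effect, the rejection rate of the unadjusted T2 comparison was 0.054, close to the nominal 0.05.

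**The case against.** The strongest reply is that the primary question, whether change over time differs between arms, is untouched. A constant sex gap drops out, and a sex main effect with one degree of freedom cannot sharpen the interaction test. That stands in full; the point concerns only the comparisons that section 4 introduces as additional.

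Other parts of the reply also stand. The 43.71 cmH2O gap is from healthy people and for S-index only. The sample size rests on MIP, for which the document gives no means by sex, so any size for MIP is an inference. Covariates and sequence details may sit in fuller documents. Section 3.4 does not say that there is a single unstratified series; a reader might infer one, but the text is merely silent.

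Two further readings are tempting and unsupported. A reader might infer that chance imbalance in sex biases the trial. Under randomisation it does not: the standard error already allows for it, and the simulated type I error stayed near 0.05. A reader might also infer that gains differ by sex because the training load is set relative to each person's own MIP. The document gives no figure for that, and even with gain made proportional to baseline, adding sex to the change comparison did not raise power (0.923 without, 0.917 with).

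What the reply does not remove is that section 4 commits to arm comparisons at each time point and names the factors of its model, with neither baseline nor sex among them.

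**Conclusion.** The point holds for the additional time-point comparisons and not for the primary group-by-time test. On S-index, between-sex variance makes up about 28% to 54% of single-visit variance for assumed within-sex SDs of 35 down to 20 cmH2O. The consequence is lost precision. The size depends on the healthy-population gap applying to people with GERD, on roughly equal numbers of men and women, and on the assumed SD. The power figures also depend on the assumed gain. For MIP the direction is plausible from the older-age cut-offs, but its size cannot be derived from the document. This is a worthwhile, nearly free improvement to secondary comparisons, not a flaw in the trial's main test.

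**What to change.** In section 4, state that the group comparisons of MIP and S-index at T2 and T3 are adjusted for the baseline value of the same outcome, with sex as a fixed factor. Baseline adjustment recovers most of the precision; sex is a small addition. The cost is one or two degrees of freedom, with no extra visits, staff or participants. It alters no participant procedure, which matters because section 5 describes the approved study as closed to further modification.

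Stratifying the envelopes by sex is optional and worth considering only if they are not yet prepared. It would need a second envelope series. Short blocks within strata would make allocation somewhat easier to predict, since section 3.4 has the principal investigator know the assignments.

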### 3.5. Participants and Eligibility Criteria

Adults aged 18–70 years with a confirmed diagnosis of gastroesophageal reflux disease by a gastroenterologist are eligible to participate (inclusion criteria). Selection and initial assessment will be done by a physiotherapist [21,22]. Exclusion criteria include pregnancy, previous gastric or duodenal surgery, systemic connective tissue diseases, tuberculosis, and diagnosed mental disorders [23].

Participants’ characteristics: The sample will comprise participants of all genders, including both males and females with diagnosed GERD, from the Attica region. The minimum sample size was determined using the G*Power software (version 3.1.9.7), based on an effect size of 1.3 for MIP reported by Fonseca et al. (2014) [24]. Based on an effect size of 1.3, a statistical power of 0.80, and an α level of 0.05, the minimum required sample size was 22 participants. Accounting for a potential 15% dropout rate, the final minimum sample size was set at 25.

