## Abstract

Gastroesophageal reflux disease (GERD) is a common chronic condition mainly caused by the dysfunction of the antireflux mechanism at the gastroesophageal junction. This is composed of the lower esophageal sphincter and the crural diaphragm. Increasing evidence suggests that diaphragmatic dysfunction and reduced inspiratory muscle strength may contribute to the persistence of GERD symptoms. Although respiratory physiotherapy has shown beneficial effects, the role of a structured inspiratory muscle training (IMT) program has not been sufficiently examined. This study aims to investigate the effects of an inspiratory muscle training program on inspiratory muscle strength and secondary clinical outcomes in individuals with GERD. A total of thirty adults with a confirmed GERD diagnosis will be enrolled in a two-arm randomized controlled trial. These volunteers will be randomly assigned either to the experimental group, which will undergo a 3-month inspiratory muscle training (IMT) using tapered flow resistive loading at 40% of maximal inspiratory pressure (MIP), or to the control group, which will receive sham IMT with a consistent low resistance. Primary outcomes will include maximal inspiratory pressure (MIP) and maximal dynamic inspiratory pressure (S-index). Secondary outcomes will assess GERD symptoms, disease-related quality of life, and pulmonary function. Measurements will be performed at baseline, at three months of intervention, and at six months from recruitment (follow-up). IMT is expected to lead to significant improvements in inspiratory muscle strength, symptom burden, and quality of life compared with sham training. This trial will provide novel evidence regarding the role of inspiratory muscle training as a non-pharmacological intervention in the management of GERD. **Trial registration:** ClinicalTrials.gov Identifier: NCT07131397.

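### The dropout-inflated minimum in section 3.5 should be 26, not 25, and the methods never mention the enrolment of 30 stated in the abstract

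*Protocol article*

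**What the plan says.** The abstract gives the planned enrolment: "A total of thirty adults with a confirmed GERD diagnosis will be enrolled in a two-arm randomized controlled trial".

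The calculation is in section 3.5. It is "based on an effect size of 1.3 for MIP", taken from a cited earlier study. With "a statistical power of 0.80, and an α level of 0.05, the minimum required sample size was 22 participants", the section then allows for losses: "Accounting for a potential 15% dropout rate, the final minimum sample size was set at 25".

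Section 3.5 does not name the test, the sidedness or the allocation ratio. Section 3.1 says only: "This study is structured as a two-arm, parallel-group randomized controlled trial". Section 4 adds: "Statistical significance will be set at an alpha level of 0.05 for all analyses". The figure of 30 appears nowhere in the methods.

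**The concern.** Two things look wrong.

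- **The inflated minimum.** Its purpose is to leave 22 evaluable participants once 15% have been lost. At the plan's own dropout rate, 25 does not do that.
- **The planned total.** The abstract commits to 30, while the only section that justifies a sample size ends at 25. A reader who compares the two cannot see how 30 was reached, or which number completeness of enrolment should be judged against.

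At stake is whether the stated sample size supports the stated power, and whether the article's later claim (section 7) of a justified calculation applies to the number that will actually be enrolled.

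**Working it through.** **Inputs.** From section 3.5: effect size 1.3, power 0.80, alpha 0.05, 22 evaluable, 15% dropout, inflated minimum 25. From the abstract: 30 enrolled. Assumed, because the article does not say: 1.3 is a between-group standardised mean difference, the test is a two-sided two-sample t test, and the arms are equal or nearly so.

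**Step 1: reproduce the 22.** Power is the probability that a noncentral t variable with n1 + n2 − 2 degrees of freedom and noncentrality d × √(n1·n2/(n1 + n2)) exceeds the two-sided 5% critical value in absolute size.

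- 10 per arm: 1.3 × √5 = 2.91, 18 df, power 78.5%.
- 11 per arm: 1.3 × √5.5 = 3.05, 20 df, power 82.6%.

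Eleven per arm is the first size to reach 80%, so the total is 22, as stated. Alternatives do not give 22: a one-sided test needs 9 per arm, two-sided alpha of 0.025 needs 13, and the normal approximation gives 10. The assumed test is therefore a reasonable reading of the calculation.

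**Step 2: the dropout step.**

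- Dividing by the retained fraction: 22 / (1 − 0.15) = 22 / 0.85 = 25.88, rounded up to 26.
- The cruder convention: 22 × 1.15 = 25.3, also rounded up to 26.

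Neither convention gives 25 unless the result is rounded down.

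**Step 3: what each total leaves.**

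| Enrolled | Expected completers at 15% dropout | Losses possible before falling below 22 |
|---|---|---|
| 25 | 25 × 0.85 = 21.25 | 3 (3/25 = 12.0%) |
| 26 | 26 × 0.85 = 22.1 | 4 (4/26 = 15.4%) |
| 30 | 30 × 0.85 = 25.5 | 8 (8/30 = 26.7%) |

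The 12.0% that 25 can absorb is below the plan's own 15%.

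**Step 4: the effect on power, same test.**

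- 21 completers (10 and 11): 80.6%.
- 22 completers (11 and 11): 82.6%.
- 25 completers (12 and 13), about what 30 enrolled would leave: 87.5%.
- All 30 completing (15 and 15): 93.0%.

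**The case against.** The strongest defence is that the two numbers are different quantities. Section 3.5 calls 25 a minimum; the abstract gives the total to be enrolled. Thirty exceeds the floor, leaves 25.5 expected completers and so covers the required 22. The slip in the floor is one participant, and 21 completers still give at least 80% power. A condensed article may also leave to the full protocol the reason why a round planned total exceeds the computed minimum. All of this stands as far as the size of the problem goes.

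It also disposes of three stronger readings that a reader might infer:

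- **That the enrolment target is undefined.** It is not: a total of 30 and a lower minimum can both hold.
- **That there are two stopping points, so that recruitment could end anywhere from 25 to 30.** Nothing in the article permits stopping at 25. Section 3.9 places the statistical analysis on the complete dataset after the study has concluded. That the principal investigator knows the allocation is a separate matter of blinding.
- **That 25 fails because an odd total cannot be split equally.** No allocation ratio is stated, and 25 is a floor, not the planned enrolment.

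The defence does not rescue the arithmetic. The plan states 22 as its minimum and 15% as its loss, and 25 does not follow from them. Nor does it supply the missing link: the article prints 30 in one place and a calculation ending at 25 in another.

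**Conclusion.** The point holds as a minor error. The inflated minimum is wrong as written: it should be 26, and 25 is one participant short, with 21.25 expected completers against the 22 required. This part rests only on the article's own figures. Separately, the total of 30 in the abstract is not reconciled with section 3.5.

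The consequence for power is small: 80.6% with 21 completers against 82.6% with 22, and about 87.5% if 30 are enrolled and 15% are lost. These percentages depend on the assumed two-sided t test, a standardised difference of 1.3 and near-equal arms. The design power is met at either total, so the defect lies in the stated numbers and not in the adequacy of the trial under its own assumptions.

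**What to change.** In section 3.5, change the inflated minimum from 25 to 26 and show the division, 22 / 0.85 = 25.9. In the same place, state the planned enrolment of 30 to which the abstract commits, and note that at the assumed 15% dropout it leaves about 25 completers and about 87.5% power for an effect size of 1.3. Name the test and sidedness behind these figures; a two-sided two-sample t test reproduces the 22. Keep 15% as the planning rate: justifying 30 by the 26.7% attrition that it could tolerate would fit a rationale to the number afterwards.

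If 30 is not the intended total, amend the abstract so that it agrees with section 3.5.

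The cost is a text correction. With 30 kept, it requires no enrolment beyond what the abstract already states, and no change to randomisation or analysis.

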### 3.6. Outcome Measurements

The outcome assessments have been selected to capture both physiological changes in inspiratory muscle performance as well as clinically significant effects on the severity and frequency of GERD symptoms. A trained physiotherapist will perform: (a) MIP (Micro RPM), according to ERS statement [25,26], (b) S-index measurement (Powerbreathe K5) [27,28] and will administer the Reflux Disease Questionnaire [29,30,31] and Reflux-Qual Short Form Questionnaire [32,33]. All measurements will be performed in random order.

Respiratory function will be assessed with the measurement of FEV1/FVC% using the Spirolab iii spirometer (Medical International Research, Inc., Rome, Italy). This will be performed by a pulmonologist with adequate training.

All measurements will be performed at three pre-specified time points: at baseline (T1), immediately after completion of the 12-week intervention (T2), and at the six-month follow-up (T3) (Table 1).

